### Inclusion criteria

Inclusion criteria are as follows: (1) inpatients aged 18–60 years with MDD diagnosed by Diagnostic and Statistical Manual of Mental Disorders, Fifth Edition, Text Revision (DSM-5-TR); (2) comorbid insomnia (PSQI >5, HAMD-17 20–35); (3) no hypnotic or acupuncture treatment in the past month; (4) no cognitive or communication disorders; (5) willingness to provide written informed consent and accept randomization; and (6) patients on a stable dose of antidepressants (e.g., escitalopram, venlafaxine, or mirtazapine) for ≥2 weeks prior to enrolment, and agreeing to maintain the same dosage during the trial, will be eligible (33).

### Exclusion criteria

Exclusion criteria are as follows: (1) suicidal tendency; (2) history of psychotic disorder, bipolar disorder, obsessive-compulsive disorder, or post-traumatic stress disorder (PTSD); (3) alcohol or substance use; (4) major medical illness (e.g., liver or kidney dysfunction, tumor, or cerebrovascular disease); (5) pregnancy or breastfeeding; and (6) inability to comply with the study protocol.

### Withdrawal criteria

Withdrawal criteria are as follows: (1) emergence of suicidal tendencies during the study; (2) occurrence of SAEs; and (3) worsening of insomnia that aggravates depressive symptoms.

### Randomization, allocation concealment and blinding

Stratified permuted block randomization will be applied to assign participants to the LA, SLA, and control groups in a 1:1:1 ratio. Stratification will be based on age (18–40 vs. 41–60 years) and gender (male vs. female), resulting in four strata: (1) males aged 18–40 years, (2) males aged 41–60 years, (3) females aged 18–40 years, and (4) females aged 41–60 years. Within each stratum, randomization sequences will be generated using permuted blocks to ensure balance until a total of 40 participants per group are enrolled (120 in total).

The randomization sequence will be generated by an independent research assistant who is not involved in the study, using GraphPad QuickCalcs, a validated web-based program for generating block randomization schemes. Allocation codes will be sealed in sequentially numbered opaque envelopes prepared by independent personnel. At enrolment, envelopes will be opened in sequence by study staff according to the order of patient visits, ensuring allocation concealment. Participants will be informed that they have an equal probability of assignment to each of the three groups.

This study will be conducted as a single-blind trial. Participants, outcome assessors, data collectors, and statisticians will remain blinded to group allocation, while acupuncturists delivering the interventions cannot be blinded due to the nature of the procedures. To maintain blinding integrity, acupuncturists will strictly follow a standardized intervention manual to minimize performance bias.

During treatment, participants will receive therapy in a closed room and will be required to wear blindfolds to prevent observation of laser irradiation. Communication among participants will be restricted, and scheduling will minimize cross-interaction. Researchers will not access unblinded data until data collection and statistical analysis are complete. Allocation concealment and restricted data access will further reduce the risk of bias, thereby strengthening the methodological rigor of the trial.

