Laser acupuncture (LA) is a non-invasive modality that applies low-dose laser stimulation to acupoints, combining principles of traditional acupuncture with modern photobiomodulation (18, 19). It is particularly suitable for needle-sensitive populations (e.g., children, the elderly) and has shown promise in improving sleep and mood symptoms by regulating neuroendocrine function and reducing inflammation (20, 21). Photobiomodulation is thought to exert its effects by stimulating mitochondrial cytochrome c oxidase, thereby enhancing cellular energy metabolism and modulating redox signaling (22–24). These changes may regulate neuroendocrine and immune pathways, contributing to the normalization of 5-HT and CORT levels relevant to sleep–wake regulation (25–27). Nevertheless, robust clinical trials investigating LA for depression-related insomnia are scarce, and its effects on underlying biological mechanisms remain poorly elucidated.

Despite its potential, significant evidence gaps exist regarding LA’s efficacy, mechanisms, and applicability in treating insomnia in MDD patients (28, 29). Few high-quality trials have specifically evaluated LA for this comorbidity, and none have comprehensively assessed its impact on sleep quality alongside biomarker changes (29, 30). Furthermore, the mechanisms by which LA may influence objective sleep outcomes and biochemical markers (e.g., 5-HT, CORT) are not yet established (31, 32). This study aims to address these gaps by evaluating the clinical efficacy and safety of LA in improving sleep quality—assessed via the Pittsburgh Sleep Quality Index (PSQI)—and depressive symptoms in MDD patients, and by exploring its potential effects on serum 5-HT and CORT levels. We hypothesize that LA will be superior to sham laser acupuncture (SLA) and standard care in improving sleep quality, reducing depressive symptoms, and modulating biomarker levels, offering a well-tolerated and non-invasive therapeutic option.

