### Patient recruitment

All participants in this trial will be recruited from the Department of Psychiatry, The Second Affiliated Hospital of XXMU, China. Recruitment will be carried out through direct approach by the research team as well as announcements posted on hospital information platforms. Interested patients may contact the study staff using the details provided and will undergo an initial eligibility screening. Those who preliminarily meet the inclusion criteria will then be interviewed face-to-face and assessed at baseline by an independent researcher who is blinded to the study objectives. After screening according to the predefined inclusion and exclusion criteria, eligible patients will be informed that they will be randomized to the LA, SLA, or control group. They will also be clearly informed of the possible benefits and risks of participation. Before enrolment, participants will voluntarily sign a written informed consent, and they will be free to withdraw from the study at any time without providing a reason.

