### Interventions

All participants will continue their stabilized antidepressant regimen throughout the study. Participants in the LA and SLA groups will additionally receive intervention according to a standardized regimen, while those in the control group will receive antidepressant medication only.

General procedures (LA and SLA groups). Participants in the intervention arms will receive treatment five days per week (with two rest days) for six weeks, totaling 30 sessions. Each session will last 20 minutes. Before treatment, participants will undergo skin cleansing, wear protective eye masks, and rest in a room maintained at >25°C. Sessions will be delivered by trained acupuncturists at The Second Affiliated Hospital of XXMU who have received protocol-specific instruction to minimize practitioner-related variability. **Figure 2** illustrates the acupoints used in this study and their locations. Paired acupoints will be stimulated bilaterally (Anmian, HT7, PC6, SP6, LR3), whereas midline acupoints will be stimulated at the midline (Baihui/GV20, Yintang/GV29). The acupoints will be used in both the LA and sham LA groups are Baihui (GV20), Yintang (GV29), Anmian (EX-HN22), Shenmen (HT7), Neiguan (PC6), Sanyinjiao (SP6), and Taichong (LR3), selected based on evidence for improving insomnia and depressive symptoms (34–36). Rescue medication is specified under “Medication use across groups” and will be applied uniformly across arms. All use will be documented in the case report form (CRF).

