SLA procedures. The sham condition used sham laser applied to the same acupoints as the LA group. Identical probes were secured with medical tape and positioned per the standardized manual, but the device delivered 0 mW output while maintaining the same indicators (lights/sounds) to preserve blinding. Session structure (per-point exposure time, total duration, number of sessions, and treatment sequence) matched the active protocol. Participants and outcome assessors were blinded; operators followed a standardized script. Regarding the validity of sham laser as a control procedure for laser acupuncture studies, in a study which evaluated the use of SLA as a control procedure by comparing verum laser with sham laser reported that treatment with verum laser was indistinguishable from sham laser and there was also no difference in the deqi-like sensations felt by study participants when comparing verum laser with sham laser. Then, the authors also analyzed the pooled findings of three RCTs that compared the use of sham laser with needle acupuncture and found that the credibility of sham laser was not different from that of needle acupuncture (39). Hence, sham laser can serve as valid placebo procedure in laser acupuncture studies.

Control group. Participants in the control arm will continue their stable antidepressant regimen without additional intervention. This group establishes a baseline comparator, enhancing the validity of between-group analyses.

Medication uses across groups. Antidepressant therapy must remain stable for ≥2 weeks before enrolment and throughout the trial. Rescue medication will be limited to oral eszopiclone 0.5 mg, to be taken as needed when insomnia persists for ≥3 consecutive nights. No other sedative–hypnotics (including benzodiazepines) will be permitted unless clinically necessary for safety; any exception requires documentation and approval by the principal investigator. All rescue-medication use will be logged (date, time, dose, indication) and reviewed regularly by the research team. If insomnia worsens alongside depressive symptoms, the participant will be withdrawn and referred for further management.

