### Blinding assessment

At the end of the treatment phase, an independent assessor will ask participants in the two intervention groups (LA and SLA) to indicate their perceived allocation by choosing one of three options: LA, SLA, or “I do not know.” Each response will be documented, and the results will be analyzed to evaluate the success of blinding.

The Bang Blinding Index (BBI) will be calculated separately for each intervention group as:

$$BBI_{i}=p_{correct,i}-p_{incorrect,i},i\in \{1,2\}$$

where *p_correct,i_* and *p_incorrect,i _*are the proportions of correct and incorrect guesses in group *i*. “I don’t know” responses are counted in the denominator but not in the numerator. A BBI value between –0.20 and +0.20 will be considered evidence of adequate blinding, whereas values approaching +1 indicate unblinding (48).

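### Participants can be blinded only between laser and sham, so comparisons with standard care on the self-reported PSQI are not participant-blind as the protocol states

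*Protocol article*

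**What the plan says.** Under Randomization, allocation concealment and blinding, the protocol article states that "Participants, outcome assessors, data collectors, and statisticians will remain blinded to group allocation". It exempts only the acupuncturists. The same section says "Participants will be informed that they have an equal probability of assignment to each of the three groups", and Patient recruitment says that "eligible patients will be informed that they will be randomized to the LA, SLA, or control group".

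Under Interventions, the two device arms are described thus: "Participants in the intervention arms will receive treatment five days per week (with two rest days) for six weeks, totaling 30 sessions". By contrast, "those in the control group will receive antidepressant medication only", and the Control group paragraph repeats it: "Participants in the control arm will continue their stable antidepressant regimen without additional intervention".

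Under Blinding assessment, the independent assessor "will ask participants in the two intervention groups (LA and SLA) to indicate their perceived allocation". Control participants are not asked, and control is not among the answers offered.

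The primary outcome is the PSQI, which the Introduction describes as measuring subjective sleep quality. The hypothesis there is that "LA will be superior to sham laser acupuncture (SLA) and standard care in improving sleep quality". Under Statistical methods, the primary analysis is a mixed ANOVA with all three arms as levels of the group factor. Post-hoc pairwise comparisons follow a significant interaction. No pairwise comparison is named as the one that establishes an effect of the laser itself.

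**The concern.** The blinding sentence claims a property that the design cannot have for two of its three pairwise comparisons. The PSQI is filled in from the participant's own view of their sleep, so a blinded assessor does not protect it from the participant's knowledge of allocation. A difference between either device arm and control therefore mixes any laser effect with expectation, attention and staff contact.

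The primary test pools all three arms. It can be significant because both device arms moved away from control, with no difference between laser and sham. If that result, or LA versus control alone, were read under the protocol's blanket statement, a non-specific effect could be taken for an effect of the laser.

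**Working it through.** **Step 1: set the sections side by side.**

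| Question | LA | SLA | Control |
|---|---|---|---|
| Told of three arms with equal chances (Patient recruitment; Randomization) | yes | yes | yes |
| Device sessions (Interventions) | 30 × 20 min = 600 min | 30 × 20 min = 600 min | none |
| Blindfold and closed room during therapy (Randomization) | yes | yes | not applicable |
| Probes with lights and sounds (Interventions) | active | 0 mW output | none |
| Asked to guess allocation (Blinding assessment) | yes | yes | no |

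A participant who knows the three arms and has no sessions knows they are in control. A participant who has sessions knows they are not. Every masking measure described can hide only active from sham. LA versus SLA can be participant-blind; LA versus control and SLA versus control cannot.

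**Step 2: reproduce the plan's own figure.** Sample size calculation gives f = 0.158, α = 0.05, power 0.80, 3 groups, 3 measurements and a minimum N of 84. It states neither the correlation ρ between measurements nor a sphericity correction; I assume ρ = 0.5 and none. For the within-between interaction:

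- λ = f² × N × m / (1 − ρ) = 0.158² × 84 × 3 / 0.5 = 12.58
- df = (3 − 1)(3 − 1) = 4 and (84 − 3)(3 − 1) = 162
- power = 0.810

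The stated 84 reproduces, so the same formula is used below.

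**Step 3: illustrate what the three-arm test picks up.** Assume the laser adds nothing and both device arms differ from control by D SD at t1 and t2. The documents give no value for D. The interaction effects are D × (1/3, 1/3, −2/3) across arms × (−2/3, 1/3, 1/3) across times. The mean square of each factor is (1/9 + 1/9 + 4/9)/3 = 2/9, so f = D × √(2/9 × 2/9) = (2/9)D. At D = 0.5, f = 0.111. N = 120 is the number randomized; N = 84 is what remains after the anticipated 30% attrition (120 × 0.70 = 84).

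| ρ | N = 84: λ | significant | N = 120: λ | significant |
|---|---|---|---|---|
| 0.3 | 4.44 | 34% | 6.35 | 49% |
| 0.5 | 6.22 | 47% | 8.89 | 65% |
| 0.7 | 10.37 | 72% | 14.81 | 88% |

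At ρ = 0.5, D = 0.3 gives 18% (N = 84) and 25% (N = 120). D = 0.711 gives 81% and 94%; that D is simply the one that returns the planning value, (2/9) × 0.711 = 0.158, and nothing in the documents says an expectation effect is that large.

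**Step 4: LA versus control alone.** With no laser effect and an allocation-knowledge shift of 0.2, 0.3 or 0.5 SD (assumed), a two-sided 0.05 comparison with 40 per arm rejects about 14%, 27% or 61% of the time instead of 5%.

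**Step 5: the joint claim.** In the Step 3 scenario (D = 0.5, ρ = 0.5), simulate t-tests on the change from t0 to the mean of t1 and t2. LA significantly beats both SLA and control in about 2.3% of trials with 28 per arm and 2.4% with 40 per arm.

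**The case against.** The best defence is that this is one over-broad sentence. The blindfold and closed room apply to those receiving therapy, the sham imitates the active device, and the blinding index is confined to LA and SLA, so the intended scope is visible. A sham arm beside an untreated arm is a legitimate design, and the sham arm exists to separate out non-specific effects. This stands: the design is not at fault. It does not rescue the sentence, which names participants without exempting control. The single-blind label does not help either, because that sentence follows it. The limitations in the Discussion cover sham credibility and contact effects of the sham but not the control arm.

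Three stronger readings are tempting, and the documents do not support them.

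- A reader might call the comparisons with standard care open-label. The protocol keeps assessors, data collectors and statisticians blinded in all arms, and nothing in the control condition prevents that. The accurate term is not participant-blind.
- A reader might take 47% or 65% as the chance of a false claim of efficacy. Those figures describe the omnibus interaction only and rest on an assumed shift and correlation. They would be the same whatever the blinding sentence said. The hypothesis is superiority over both SLA and standard care, and Step 5 shows that this joint result is rare when the laser adds nothing.
- A reader might infer that the sponsor will present superiority over standard care as blinded evidence. No section says so; the wording merely leaves room for it.

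**Conclusion.** The point holds as a misstatement about blinding with a consequence for interpretation. Participant blinding is claimed for all arms but is possible for one of three pairwise comparisons, and the other two bear on a self-reported primary outcome. This conclusion needs no numerical assumption.

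The size of any resulting bias cannot be derived from the documents. Under an assumed 0.5 SD non-specific shift and ρ from 0.3 to 0.7, the three-arm interaction is significant in 34% to 88% of trials across the two sample sizes. It cannot by itself support a statement about the laser, and neither can LA versus control. LA versus SLA is unaffected, and a conclusion that requires LA to beat both comparators is well protected. The correction should be made, but it does not undermine the trial.

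**What to change.** - **Randomization, allocation concealment and blinding:** state that participants are blinded between LA and SLA only, that control participants are aware of their allocation, and that outcome assessors, data collectors and statisticians are blinded in all three arms.
- **Statistical methods:** state that a laser-specific effect is concluded only from LA versus SLA, and not from the three-arm interaction or from LA versus control alone. State that comparisons with standard care are not participant-blind and include expectation, attention and contact effects.
- **Discussion, limitations:** add the same point about the control arm.

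The hypothesis in the Introduction needs no change, since it makes no claim about blinding. The control arm stays, and no new data or participants are required. The cost is wording, plus one real concession: superiority over standard care cannot be presented as participant-blinded evidence.

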### Interventions

All participants will continue their stabilized antidepressant regimen throughout the study. Participants in the LA and SLA groups will additionally receive intervention according to a standardized regimen, while those in the control group will receive antidepressant medication only.

General procedures (LA and SLA groups). Participants in the intervention arms will receive treatment five days per week (with two rest days) for six weeks, totaling 30 sessions. Each session will last 20 minutes. Before treatment, participants will undergo skin cleansing, wear protective eye masks, and rest in a room maintained at >25°C. Sessions will be delivered by trained acupuncturists at The Second Affiliated Hospital of XXMU who have received protocol-specific instruction to minimize practitioner-related variability. **Figure 2** illustrates the acupoints used in this study and their locations. Paired acupoints will be stimulated bilaterally (Anmian, HT7, PC6, SP6, LR3), whereas midline acupoints will be stimulated at the midline (Baihui/GV20, Yintang/GV29). The acupoints will be used in both the LA and sham LA groups are Baihui (GV20), Yintang (GV29), Anmian (EX-HN22), Shenmen (HT7), Neiguan (PC6), Sanyinjiao (SP6), and Taichong (LR3), selected based on evidence for improving insomnia and depressive symptoms (34–36). Rescue medication is specified under “Medication use across groups” and will be applied uniformly across arms. All use will be documented in the case report form (CRF).

**Figure 2 f2:**
[figure not shown]
Illustration of the acupoints used in this study. Baihui (GV20): on the vertex of the head, 5 inches posterior to the anterior hairline at the midpoint of the line connecting the apex of both ears; Yintang (GV 29): on the forehead, at the midpoint between the medial ends of the eyebrows; Anmian (EX-HN22): on the posterior aspect of the ear, midway between Fengchi (GB20) and Yifeng (SJ17); Shenmen (HT7): on the wrist, at the transverse crease, in the depression on the radial side of the tendon of flexor carpi ulnaris; Neiguan (PC6): on the forearm, 2 inches above the transverse crease of the wrist between the tendons of palmaris longus and flexor carpi radialis; Sanyinjiao (SP6): on the medial side of the lower leg, 3 inches above the prominence of the medial malleolus, posterior to the medial border of the tibia; Taichong (LR3): on the dorsum of the foot, in the depression distal to the junction of the first and second metatarsal bones.

LA procedures. Participants in the LA group will receive low-dose photobiomodulation at prespecified acupoints using the xS-998D06 Semiconductor Laser Acupoint Therapeutic Apparatus (Nanjing Xiaosong Medical Devices Co., Ltd.). The device operates at 650 nm in pulsed mode (50 Hz; 50% duty cycle; stability ≈92%). Dosimetry: reflecting device stability, the on-period output power is 2.3 mW and the time-averaged effective power is 1.15 mW. Each acupoint is irradiated for 20 minutes, delivering 1.38 J per point. The beam spot is standardized with a spacer cap that defines an effective treated area of 1.0 cm², yielding an energy density of 1.38 J/cm². We selected a 1.0 cm² spot to cover the typical footprint of a single acupoint while minimizing spillover, consistent with commonly reported PBM fluence ranges (37). In this trial we apply 12 probes simultaneously, one per acupoint, secured with medical adhesive tape to ensure identical dosing and timing across points and to enhance reproducibility; the total session energy is 16.56 J (1.38 J × 12 acupoints). These low-dose parameters comply with Class 3R laser safety guidance and are supported by prior studies linking photobiomodulation to modulation of 5-HT, sleep quality, and depressive symptoms (38, 39).

SLA procedures. The sham condition used sham laser applied to the same acupoints as the LA group. Identical probes were secured with medical tape and positioned per the standardized manual, but the device delivered 0 mW output while maintaining the same indicators (lights/sounds) to preserve blinding. Session structure (per-point exposure time, total duration, number of sessions, and treatment sequence) matched the active protocol. Participants and outcome assessors were blinded; operators followed a standardized script. Regarding the validity of sham laser as a control procedure for laser acupuncture studies, in a study which evaluated the use of SLA as a control procedure by comparing verum laser with sham laser reported that treatment with verum laser was indistinguishable from sham laser and there was also no difference in the deqi-like sensations felt by study participants when comparing verum laser with sham laser. Then, the authors also analyzed the pooled findings of three RCTs that compared the use of sham laser with needle acupuncture and found that the credibility of sham laser was not different from that of needle acupuncture (39). Hence, sham laser can serve as valid placebo procedure in laser acupuncture studies.

Control group. Participants in the control arm will continue their stable antidepressant regimen without additional intervention. This group establishes a baseline comparator, enhancing the validity of between-group analyses.

Medication uses across groups. Antidepressant therapy must remain stable for ≥2 weeks before enrolment and throughout the trial. Rescue medication will be limited to oral eszopiclone 0.5 mg, to be taken as needed when insomnia persists for ≥3 consecutive nights. No other sedative–hypnotics (including benzodiazepines) will be permitted unless clinically necessary for safety; any exception requires documentation and approval by the principal investigator. All rescue-medication use will be logged (date, time, dose, indication) and reviewed regularly by the research team. If insomnia worsens alongside depressive symptoms, the participant will be withdrawn and referred for further management.

